### Blinding

Before and during the study, patients will not be informed about the treatment allocation of their hospital. Therefore, patients will be blinded during the study period. After the study patients will be informed whether or not the intervention was received. Due to the nature of the intervention and due to the cluster randomization, the researchers and the treating health care professionals will not be blinded. However, all measurements, except for the secondary outcome measurement modified Rankin Scale (mRS), will be completed by the patients without assistance of the researchers or treating health care professionals. As such, outcome measurements will be administered in a blinded manner.

### Sample size

Since no USER-Participation-R data are available concerning the participation levels of our target group, we based our sample size calculation on Cohen’s effect size as benchmark for assessing the relative magnitude of differences in participation level between the treatment arms. Although a Cohen’s effect size of 0.35 can be defined as between small and medium, such a difference in mean participation scores may be clinically important. Therefore, it was considered necessary to detect this difference in participation level between both treatment arms. A sample size of six clusters per treatment group (12 clusters in total) with 36 individuals per cluster (216 patients per treatment group; 432 patients in total) achieves 81% power to detect an effect size of 0.35 when the intracluster correlation is 0.01 using a two-sided t-test based on the number of clusters, with a significance level of 0.05 [21]. Anticipating on a 15% attrition rate in each center, we will include (36 / 0.85 =) 43 patients per center, resulting in 258 patients per treatment group and 516 patients in total.

### Intervention group

In the intervention group, patients receive an intervention that consists of a face-to-face consultation of approximately 60 min at the outpatient clinics of the neurology department in addition to usual care. This intervention will take place at approximately 6 weeks after the stroke with a maximum range of 2 weeks earlier or later. A maximum of one follow-up session after the initial consultation may be proposed by the nurse if needed, but this is not obligatory. When more follow-up sessions seem to be needed, referral for specialized (rehabilitation) care will be advised; which specialized care that will be, depends on the problems experienced and the local health care situation. The consultation will be executed by a specialized nurse, nurse practitioner or physician assistant who is experienced in and currently performs outpatient care for patients with stroke at the participating center; hereinafter referred to as ‘nurse’. If a nurse is not available in an eligible center, one of the researchers (JS) will perform the intervention.

The intervention includes:
a structured screening for cognitive and emotional problems using sensitive instruments: the Checklist for Cognitive and Emotional Consequences following stroke (CLCE-24), the Montreal Cognitive Assessment (MoCA) (if the MoCA has been performed at an earlier moment after stroke and the score was ≥26, the MoCA does not need to be repeated) and the Hospital Anxiety and Depression Scale (HADS);a structured screening for restrictions in participation by the USER-Participation-R;self-management support consisting of the following elements: a) providing timely and individualized oral and written information about stroke and its possible cognitive and emotional sequelae, b) measuring self-efficacy by the Dutch General Self-Efficacy Scale (GSES) and providing patient-tailored guidance, c) achieving shared-decision making and d) providing contact details for possible additional questions or problems;a decision tool for referral to rehabilitation services based on the results of the screening instruments. Generally, if patients experience one or more participation restriction(s), as measured by the USER-Participation-R, due to the recent ischemic stroke, referral to rehabilitation services will be indicated, but is not obliged. Besides, a close cooperation with the physiatrist will be advised, in order to decide upon optimal follow-up care.

All nurses will attend a single, four-hour training to be able to perform the intervention; this training will be given by a researcher (JS). Besides, a manual will be handed out describing all components in detail. Due to the blinded nature of the trial, the manual will be published after study completion. After this training, the first intervention will be observed by the researcher. During the study, a researcher (JS) is available for consultation and further questioning on a weekly basis.

### Control group

In the control group, patients will receive care as usual according to the current protocol of the participating hospital. The local protocol probably varies among the various hospitals.

### Outcomes

Since the study has three objectives, the paragraphs ‘Outcomes’, ‘Data Collection’ and ‘Statistical Analysis’ are sorted accordingly.

### Primary outcome measure

#### Clinical effectiveness

The primary outcome measure will be the level of participation measured with the USER-Participation-R [22]. The USER-Participation-R will be completed at 6 weeks (T1), 3 months (T2) and 12 months (T3) after stroke.

### Secondary outcome measures

#### Clinical effectiveness

The following secondary outcome measures will be used: cognitive and emotional complaints (CLCE-24), depression and anxiety (HADS), quality of life (Five-Dimensional EuroQol (EQ-5D-5L)), global health (Patient Reported Outcome Measurement Information System (PROMIS) Global-10), self-efficacy (GSES) and physical disability (mRS) [23–28]. These questionnaires will be completed at T1, T2 and T3.

#### Cost-effectiveness

Quality of life will be measured with the Five-Dimensional EuroQol (EQ-5D-5L). Costs will be assessed with the Medical Consumption Questionnaire (MCQ) and the Productivity Cost Questionnaire (PCQ) [29–31]. The following cost categories will be distinguished: intervention costs, health care costs, patient and family costs and costs outside the health care sector (productivity). Data for the economic evaluation will be collected at T1, T2 and T3.

#### Process evaluation

The implementation of the intervention will be examined by a process evaluation. This process evaluation will consist of a mixed methods study, i.e. using both quantitative and qualitative methods, and will be conducted alongside the randomized controlled trial.

### Data collection

#### Demographic and stroke characteristics

In both groups, the electronic patient record will be used to complete age, sex, medical history and stroke characteristics at baseline (T0). Other demographic characteristics, such as level of education, marital status or having a partner and working status, will be registered in the questionnaires that are completed by the patients at T1.

#### Clinical effectiveness

In the centers that are randomized to the intervention group, patients will visit the neurologic outpatient clinic for the intervention approximately 6 weeks after their stroke. Patients will be asked to complete the questionnaires sent by mail and bring them along to the consultation (see Table 1). The results from the USER-Participation-R, CLCE-24, HADS and GSES will be used by the nurse for additional questioning and individualized counselling; however, the results of the completed questionnaires will not be changed. Besides, the MoCA will be completed by the nurse during the consultation (T1). The other questionnaires will be collected during the consultation, but will only be used for research purposes. Follow-up moments at T2 and T3 include questionnaires that will be sent by mail or email (see Table 1).

**Table 1 Tab1:** Overview of baseline and follow-up measurements

	measurements	baseline (T0)	6 weeks (T1)	3 months (T2)	12 months (T3)
**Demographic**					
age		x			
sex		x			
education		x			
marital status / partner		x			
working status		x			
medical history		x			
**Stroke-related**					
stroke characteristics	type, hemisphere, NIHSS at admission	x			
length of hospital admission		x			
disability at discharge	mRS	x			
**Screening instruments (intervention group)**					
participation	USER-Participation-R^a^		x^a^		
cognitive and emotional complaints	CLCE-24^a^		x^a^		
cognitive disorders	MoCA^a^(not for patients in the usual care group)		x^a^		
symptoms of depression and anxiety	HADS^a^		x^a^		
self-efficacy	GSES^a^		xª		
**Primary outcome**					
participation	USER-Participation-R^a^		x^a^	x	x
**Secondary outcomes**					
cognitive and emotional complaints	CLCE-24^a^		x^a^	x	x
symptoms of depression and anxiety	HADS^a^		x^a^	x	x
physical disability	mRS	x		x	x
self-efficacy	GSES^a^		x^a^	x	x
global health	PROMIS Global-10		x	x	x
patient satisfaction with stroke-care	customized version of SASC-19			x	
quality of life	EQ-5D-5L		x	x	x
cost questionnaires	MCQ PCQ		x	x	x

*NIHSS* National Institute of Health Stroke Score; *mRS* Modified Rankin Scale; *USER-Participation-R*, Restriction subscale of the Utrecht Scale for Evaluation of Rehabilitation on the level of Participation; *CLCE-24* Checklist for Cognitive and Emotional Consequences following stroke; *MoCA* Montreal Cognitive Assessment; *HADS* Hospital Anxiety and Depression Scale; *GSES* Dutch adaptation of the General Self-Efficacy Scale; *PROMIS Global-10* Patient Reported Outcome Measurement Information System; *SASC-19* Satisfaction with Stroke-Care; *EQ-5D-5L* Five-Dimensional EuroQol; *MCQ*, Medical Consumption Questionnaire; *PCQ* Productivity Cost Questionnaire

^a^
*those questionnaires will be used as both a screening instrument and an outcome measurement*

In the centers that are randomized to usual care, patients will be asked to complete the questionnaires at T1, T2 and T3 (Fig. 1). These questionnaires will be sent to the patient by mail or by email (see Table 1).

**Fig. 1 Fig1:**
[figure not shown]
Flowchart of ECO-stroke trial procedure

The following measurements will be completed:
*Restriction subscale of the Utrecht Scale for Evaluation of Rehabilitation – Participation (USER-Participation-R)*

To measure restrictions in participation, the USER-Participation-R will be performed. This is a patient-reported subscale of the USER-Participation measuring experienced restrictions on 11 domains of participation, such as household activities, return to work or social activities [22]. The USER-Participation-R will be completed by the patient at home.
2.*Checklist for Cognitive and Emotional Consequences following stroke (CLCE-24)*

Subjective cognitive and emotional complaints will be measured with the CLCE-24 [23]. This checklist consists of 24 items concerning several cognitive and emotional domains. For each item the presence or absence can be scored. The CLCE-24 will be administered by the nurse in the intervention group at T1. For the control group at T1, and for all patients at T2 and T3 a self-reported CLCE-24 will be completed by the patient at home.
3.Montreal Cognitive Assessment (MoCA)

The MoCA will be administered to screen for objective cognitive impairments [29]. The MoCA assesses eight cognitive domains with a total score ranging from zero to 30. The MoCA will be administered by the nurse in the intervention group at T1, unless the MoCA has been performed at an earlier moment after stroke and the score was ≥26. The MoCA will not be administered in the control group.
4.*Hospital Anxiety and Depression Scale (HADS)*

The HADS will be administered to measure symptoms of depression and anxiety [24]. This scale consists of 14 items; symptoms of anxiety and depression will be measured by seven items each. Each item is rated on a four-point scale. The total scores of each subdomain range from zero to 21 resulting in a combined maximum score of 42. The HADS will be completed by the patient at home.
5.*Five-Dimensional EuroQol (EQ-5D-5L)*

To measure generic health related quality of life the EQ-5D-5L will be administered. The five dimensions are: mobility, self-care, usual activities, pain or discomfort and anxiety or depression. Each dimension can be rated on a five-point scale: ‘no problems’, ‘slight problems’, ‘moderate problems’, ‘severe problems’ and ‘extreme problems’ [25]. The EQ-5D-5L will be completed by the patient at home.
6.*Patient Reported Outcome Measurement Information System (PROMIS) Global-10*

To measure medical global health the PROMIS Global-10 will be administered [26]. This ten-item-questionnaire assesses global health in terms of physical health, mental health, social health, pain, fatigue and overall perceived quality of life. These ten items are to be scored on a five-point scale. The PROMIS Global-10 will be completed by the patient at home.
7.*Dutch adaptation of the General Self-Efficacy Scale (GSES)*

To measure the level of general self-efficacy the GSES will be administered [27]. The GSES consists of ten items scored on a four-point scale, ranging from ‘totally wrong’ to ‘totally true’. The GSES will be completed by the patient at home.
8.*Modified Rankin Scale (mRS)*

The mRS will be used to measure the level of disability in daily activities. The score ranges from zero (‘no symptoms at all’) to five (‘severe disability’) and six (‘dead’) [28]. The mRS will be completed by telephone with the researcher or by the nurse.
9.*National Institute of Health Stroke Scale (NIHSS)*

Stroke severity in terms of physical disability will be measured with the NIHSS [30]. The NIHSS consists of 15 items and ranges from 0 to 42. The NIHSS will be completed by the treating physician at admission in the hospital at stroke onset.

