### Process evaluation

A process evaluation was developed in accordance with the framework of the Medical Research Council and consists of the following parts: [33].
*Reach and Dose of the Intervention*

The reach of the intervention is defined as the number of patients actually included in the study, divided by the total number of patients that were screened for eligibility. This information will be registered in a screening log.

The dose of the intervention is defined as the number of patients actually receiving the intervention, divided by the total number of patients included in the study. This information will be registered in the electronic case report form (eCRF).
2.*Fidelity to the Intervention Protocol*

The fidelity is defined as the adherence to the original intervention protocol. The fidelity to the following components of the intervention will be registered. First, the protocol prescribes that the intervention should be performed within four to 8 weeks after the ischemic stroke. The timing of the intervention will be registered in the eCRF. Second, patient charts and eCRF will be used to register if the patient brought the completed questionnaires to their appointment. Third, in the patient charts will be registered if the nurse completed the screenings instruments during the consultation. Fourth, in the eCRF will be registered if the nurse provided individualized information and if shared decision making took place. Fifth, the nurse will register in the eCRF if the intervention could be completed within the estimated time. In addition, in a focus group interview, the nurses will be asked for experience with the application of the intervention in their daily care and the adherence to the intervention protocol for more profound understanding of possible deviations from the protocol.
3.*Contextual Factors*

Contextual factors that might affect implementation are measured by the Barriers and Facilitators Assessment Instrument (BFAI) [34]. The BFAI will be completed by the nurse after he/she delivered the intervention to ten study patients and before the focus group interview takes place. During this interview, additional information will be gathered to get a more profound understanding of the barriers and facilitators nurses reported in the BFAI during this interview for further questioning.
4.*Patient Satisfaction*

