### Statistical analysis

#### Clinical effectiveness

Descriptive statistics will be used to describe baseline data and outcomes. Normal Q-Q Plots and the Shapiro-Wilk test will be performed to test for normality. In normally distributed continuous variables, means and standard deviations will be used. Non-normally distributed variables and ordinal variables will be expressed by medians and interquartile ranges. Categorical variables will be described by counts and percentages. Missing data will be handled by multiple imputations. Two-sided 95% confidence intervals (CI) will express the statistical uncertainty; a two-sided *p*-value < 0.05 will be considered statistically significant. Multiple testing will not be corrected for. An intention-to-treat principle will be applied to the statistical analyses.

We will perform the main analysis of the primary outcome on the change (delta) USER-Participation-R scores between 6 weeks and 12 months and a sensitivity analysis on the observed USER-Participation-R scores at 12 months. We will use a linear mixed effects model with center as a random effect and treatment arm as a fixed effect for both analyses. In addition, we will analyze the three repeated measurements (6 weeks, 3 months and 12 months) of USER-Participation-R scores using a single linear mixed effects model with nested random effects for patients within centers and treatment arm as a fixed effect.

For the continuous secondary outcome parameters (CLCE-24, HADS, PROMIS-10 and GSES) we will use the same statistical modelling approach as described above.

The continuous secondary outcome parameter SASC-19 will be analyzed using an unpaired t-test.

With regard to the ordinal scores on the mRS we will calculate the within-group median change scores as the 50th percentile of all individual differences (change from baseline to 1-year outcome assessment). Point estimate and 95% CI of the median difference in change scores between treatment groups will be calculated using the Hedges-Lehmann method [36]. Between-group difference in change scores will be analyzed using the Mann-Whitney test.

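### The protocol contradicts itself on who completes the CLCE-24 at T1 in the intervention arm; if the nurse does, the planned change-from-T1 analysis of this secondary outcome carries a mode difference between arms

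*Protocol article*

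**What the plan says.** All references are to the protocol article.

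- **Data collection, item 2 (CLCE-24).** "The CLCE-24 will be administered by the nurse in the intervention group at T1". The next sentence sets the mode for everyone else: "For the control group at T1, and for all patients at T2 and T3 a self-reported CLCE-24 will be completed by the patient at home".
- **Table 1, footnote a.** The T1 CLCE-24 carries the footnote "those questionnaires will be used as both a screening instrument and an outcome measurement", so the T1 score is outcome data as well as screening content.
- **Blinding.** All measurements other than the mRS "will be completed by the patients without assistance of the researchers or treating health care professionals". The section concludes from this that outcomes are collected blind.
- **Data collection, Clinical effectiveness (intervention centers).** "Patients will be asked to complete the questionnaires sent by mail and bring them along to the consultation". The CLCE-24 is then listed with the USER-Participation-R, HADS and GSES as results the nurse uses for further questioning, with the completed forms left unaltered. Only the MoCA is named there as completed by the nurse.
- **Statistical analysis, Clinical effectiveness.** The main analysis of the primary outcome is the change from 6 weeks to 12 months. A sensitivity analysis uses the observed 12-month score, and a further mixed model uses all three time points with treatment arm as the only named fixed effect. The section then says: "For the continuous secondary outcome parameters (CLCE-24, HADS, PROMIS-10 and GSES) we will use the same statistical modelling approach".

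**The concern.** Two adjacent sentences in the CLCE-24 item assign different modes by arm at T1, so this does not look like a slip of wording. Under that item, the intervention arm goes from an interview with the unblinded nurse who delivers the intervention to a form filled in at home. The control arm uses the home form throughout. An analysis of change from T1 cannot separate that switch from an effect of the intervention.

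Cognitive and emotional complaints are what the intervention screens for, so a change in CLCE-24 would be read as direct evidence of benefit or harm. If the score counts complaints present, a nurse who elicits more of them than the form does (b > 0) makes the intervention arm appear to improve. A nurse who elicits fewer makes it appear to worsen. A larger sample narrows the interval around the wrong value.

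The conflict between sections also matters by itself: a center cannot tell from the text which T1 CLCE-24 belongs in the research dataset.

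**Working it through.** **1. Mode by arm and time, under the CLCE-24 item**

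| | T1 | T2 | T3 |
|---|---|---|---|
| Intervention | nurse | self | self |
| Control | self | self | self |

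Under the Blinding section and the account of the mailed questionnaires, every cell would be self. The two readings differ only in the intervention arm at T1.

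**2. Effect on each planned CLCE-24 analysis.** Let b be the mean nurse-administered minus self-reported score at T1.

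- *Change, T3 − T1 (main).* The intervention arm's T1 mean is raised by b and nothing else moves. Expected contrast = true effect − b.
- *Observed 12-month score (sensitivity).* Both arms self-report, so there is no b term.
- *Three time points, arm the only fixed effect named.* With complete data and equal weights, the arm estimate averages the three between-arm differences. One of them contains +b, so the shift is b/3, opposite in sign to the shift in the change analysis.

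Using the T1 score as a covariate would not solve this, because mode and arm coincide completely at T1.

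**3. The plan's own figure.** The Sample size section gives 6 clusters per arm, 36 patients per cluster, ICC 0.01, effect size 0.35, two-sided alpha 0.05, and a t-test based on the number of clusters.

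- Design effect = 1 + 35 × 0.01 = 1.35
- n per arm = 6 × 36 = 216
- Standard error in SD units = √(2 × 1.35 / 216) = √0.0125 = 0.1118
- Noncentrality = 0.35 / 0.1118 = 3.13, with 2 × 6 − 2 = 10 degrees of freedom
- Power = 80.5%, against 81% stated. It reproduces.

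This figure concerns the primary outcome. It is used here only to set the precision for the next step.

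**4. Illustration of what b could do.** The documents give no b and no T1–T3 correlation (ρ). The assumptions are: no true effect, b in units of the single-time SD, equal SDs at T1 and T3, ICC 0.01 for the change score, 216 patients per arm and 10 degrees of freedom.

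SD of change = √(2(1 − ρ)), which is 1.000 for ρ = 0.5 and 0.775 for ρ = 0.7. Noncentrality = (b / SD of change) / 0.1118.

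| Assumed b (SD) | Noncentrality, ρ = 0.5 | P(significant) | Noncentrality, ρ = 0.7 | P(significant) |
|---|---|---|---|---|
| 0 | 0 | 5% | 0 | 5% |
| 0.1 | 0.89 | 13% | 1.15 | 18% |
| 0.2 | 1.79 | 37% | 2.31 | 55% |
| 0.3 | 2.68 | 68% | 3.46 | 88% |

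The probabilities are the same for negative b, with the direction reversed.

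**The case against.** The strongest reply is that the bias is conditional and already partly guarded against. If centers follow the account of the mailed questionnaires, a self-completed T1 form exists in both arms, b drops out, and only the wording is at fault. Even if the nurse-administered score is used, the 12-month comparison is planned and contains no mode difference, so a discrepancy between the two analyses would be visible. Both points stand. They limit the consequence but leave two problems: the text does not say which T1 score is the outcome value, and the analysis labelled as main is the exposed one.

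Three stronger readings are tempting, and the documents do not support them.

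- *The same problem affects the primary outcome, HADS and GSES.* A reader might infer this from the fidelity item in the Process evaluation section, which records "if the nurse completed the screenings instruments during the consultation". But the Data collection items say that the USER-Participation-R, HADS and GSES are each completed by the patient at home, and that completed forms are not altered. The fidelity item is adequately explained by the MoCA and CLCE-24, the two instruments those items assign to the nurse.
- *The bias is a known, large share of the effect the trial is sized for.* Dividing 0.1 and 0.3 SD by 0.35 gives 29% and 86%, but the numerator is assumed and the denominator is the target for participation. The trial is not sized on the CLCE-24, and b = 0 is not excluded.
- *The bias is certain.* It follows only if the CLCE-24 item governs.

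**Conclusion.** The point holds within limits and should be fixed. What is certain is the contradiction: the CLCE-24 item cannot be squared with the Blinding section or with the account of the mailed T1 questionnaires. What is conditional is the bias. If the CLCE-24 item governs, the main CLCE-24 analysis is off by the whole of b, and the three-timepoint model by about b/3 in the other direction, under complete data and equal weights. Neither the size nor the sign of b can be had from the documents, so the 13% to 88% range shows only what assumed values of 0.1 to 0.3 SD would do.

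The scope is one secondary outcome. The primary result and the 81% power are not affected.

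**What to change.** 1. Align the CLCE-24 item, the Blinding section and the account of the mailed questionnaires. State that the T1 research value of the CLCE-24, in both arms, is the form the patient completes at home before any consultation.
2. Keep any nurse-administered CLCE-24 as part of the intervention, and keep its score out of the outcome data.
3. Where no self-completed T1 form exists in the intervention arm, make the 12-month self-reported between-arm comparison the main CLCE-24 analysis. Do not run the change analysis for this outcome, and restrict its repeated-measures model to T2 and T3.
4. Because the plan handles missing data by multiple imputation, state that the intervention arm's T1 CLCE-24 is not to be imputed from nurse-administered scores. Otherwise the mode difference returns through the imputation model.

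The cost is wording in three places, plus one self-report form in a T1 mailing the protocol already describes; the control arm already uses that form. The content of the consultation does not change. A self-completed T1 score that was not collected before the visit cannot be recovered afterwards, so the clarification is worth most while T1 forms are still being sent out.

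### The mRS, the only outcome not self-completed at 3 and 12 months, may be scored by the nurse who gave the consultation or by an unblinded researcher, with no rule by arm or time point

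*Protocol article*

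**What the plan says.** All places are in the protocol article.

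- **Data collection, Clinical effectiveness, item 8 (mRS):** "The mRS will be completed by telephone with the researcher or by the nurse". Nothing says which rater or mode applies to which arm or time point.
- **Intervention group:** "The consultation will be executed by a specialized nurse, nurse practitioner or physician assistant", and the section then adopts 'nurse' as its term for that person. The fallback is: "If a nurse is not available in an eligible center, one of the researchers" delivers it.
- **Blinding:** "the researchers and the treating health care professionals will not be blinded". The section then states that "all measurements, except for the secondary outcome measurement modified Rankin Scale (mRS), will be completed by the patients without assistance" from those staff, and concludes: "As such, outcome measurements will be administered in a blinded manner".
- **Table 1:** the mRS is a secondary outcome, marked at baseline (discharge), 3 months (T2) and 12 months (T3).
- **Statistical analysis, Clinical effectiveness:** mRS change from baseline to 1 year is compared between groups by a Mann-Whitney test, with an estimate and confidence interval for the median difference in change.
- **Data collection, item 2 (CLCE-24):** "The CLCE-24 will be administered by the nurse in the intervention group at T1". Controls at T1, and all patients at T2 and T3, complete it themselves.

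**The concern.** The mRS is a graded judgement made by a rater. The wording lets the person who delivered the intervention grade the disability of the patients who received it. That situation cannot arise in a usual care center, where nobody delivers the intervention. Because rater and mode are left open, the arms could also differ in who scores and in whether scoring is by telephone.

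The protection the protocol offers elsewhere is patient self-completion, and it does not reach this outcome. The Discussion's answer to unblinded professionals rests on most outcomes being patient-reported, which again leaves the mRS out. An apparent mRS difference would then be hard to separate from a rater effect.

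**Working it through.** **1. Who can be the rater.** Item 8 names two raters, the researcher and the nurse. Under Intervention group, the nurse delivers the consultation, and a researcher does so where a center has no nurse. Under Blinding, neither group is blinded. Both permitted raters are therefore unblinded, and either may have delivered the intervention. The Discussion adds that most hospitals have one professional in outpatient stroke care, so where a nurse scores the mRS in an intervention center, it will often be the nurse who gave the consultation.

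**2. Which outcomes are exposed.** At T2 and T3 the USER-Participation-R, CLCE-24, HADS, EQ-5D-5L, PROMIS Global-10, GSES, the cost questionnaires and (T2 only) the SASC-19 are completed by the patient. Only the mRS is not. At T1 the CLCE-24 is also staff-administered, in the intervention arm alone. The Blinding section, which names the mRS as the sole exception, does not match item 2.

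**3. The blinding conclusion.** The section excepts the mRS from unassisted completion and then concludes, for outcome measurements in general, that administration is blinded. The conclusion holds at most for self-completed measures.

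**4. Whether the analysis absorbs it.** Baseline mRS is disability at discharge, before the consultation. A rater effect that arises afterwards stays in the change score. The Mann-Whitney comparison has no center or rater term.

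**5. How sensitive the test is (illustration).** The protocol gives no mRS figure to reproduce, so everything here except the 216 per arm (Sample size) is assumed:
- no true effect and no clustering;
- two discharge distributions over grades 0/1/2/3: A = 25/40/25/10% and B = 15/45/30/10%;
- true change of -1/0/+1 in 30/55/15%, with grades kept within 0-5;
- a share q of intervention patients scored one grade too low at 12 months, where the grade is above 0;
- 2,000 simulated trials per row, two-sided 5% Mann-Whitney test on change.

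| q | A | B |
|---|---|---|
| 0% | 5.4% | 4.7% |
| 5% | 8.7% | 8.2% |
| 10% | 18.3% | 20.4% |
| 15% | 33.0% | 38.1% |
| 20% | 52.5% | 59.0% |

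Entries are rejection rates. Simulation error is about sqrt(0.05 × 0.95 / 2000) = 0.5 percentage points in the first row.

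**6. Effect on the estimate.** Take the same change distribution, ignore the floor at 0 and set q = 10%. Intervention changes become:
- -2: 0.1 × 0.30 = 0.03
- -1: 0.9 × 0.30 + 0.1 × 0.55 = 0.325
- 0: 0.9 × 0.55 + 0.1 × 0.15 = 0.51
- +1: 0.9 × 0.15 = 0.135

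P(intervention < control) = 0.03 × 1 + 0.325 × 0.70 + 0.51 × 0.15 = 0.334. P(intervention > control) = 0.51 × 0.30 + 0.135 × 0.85 = 0.268. Both are below one half, so the median pairwise difference stays at 0. The p-value is sensitive at this level of misrating; the planned point estimate is not.

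**7. What does not change.** The sample size calculation concerns the USER-Participation-R. With design effect 1 + 35 × 0.01 = 1.35, noncentrality 0.35 / sqrt(2 × 1.35 / 216) = 3.13 and 10 degrees of freedom, power is 80.5%, in line with the stated 81%. No power, sample size or alpha figure depends on the mRS rater.

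**The case against.** The protocol is open about this: the Blinding section names the mRS as the exception, and the Discussion lists unblinded professionals as a limitation. The outcome is secondary. The sentence in item 8 covers all time points, so the nurse may be meant for discharge and the telephone call for follow-up; the article describes T2 and T3 as mailed or emailed questionnaires and schedules no nurse visit then. A journal article may also leave rater assignment to the full protocol.

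Much of this stands. It makes the point small, and nurse scoring at T2 or T3 is permitted rather than stated. It does not remove the point: the text as published allows that scoring, and disclosing the exception does not make the general conclusion on blinding true of the mRS.

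A reader might also infer more than the documents support:
- **That the mRS is the only rater-scored outcome.** The CLCE-24 is nurse-administered at T1 in the intervention arm.
- **That the bias favors the intervention.** This is plausible for a rater with a stake in the result, but a nurse who has just screened for deficits could also record more disability. No text settles it.
- **That the bias can be sized against the effect of 0.35.** That effect belongs to the USER-Participation-R, and a mean shift over a standard deviation is not the scale of the planned mRS analysis.
- **That a neutral rater already exists on the team.** Researchers are mentioned in the plural, but the group is described as unblinded and nobody free of training and delivery duties is identified.
- **That the mRS result would be uninterpretable.** An openly unblinded secondary outcome can be read with caution.

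**Conclusion.** The concern holds as a minor, inexpensive improvement. The protocol permits the mRS at T2 and T3 to be scored by the person who delivered the intervention or by an unblinded researcher, without a rule by arm or time point, and its general statement on blinded administration cannot apply to this outcome. The consequence is a risk of rater bias and of a rater or mode difference between arms, confined to one secondary outcome. The primary outcome is completed by the patient at home and is untouched.

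Direction and size are not established. The simulated false-positive rates (8-9% at 5% misrating, 18-20% at 10%) rest on assumed grade distributions, no clustering and an assumed one-sided shift. They show that the test is sensitive to rater effects, not that effects of that size will occur.

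**What to change.** 1. For T2 and T3, remove the nurse as an alternative mRS rater. Use the researcher telephone call already planned, with one fixed script, in both arms.
2. Work from a study-number list that does not show center. Where the team allows, the caller should be a researcher who neither trained nurses nor delivered consultations; the documents do not show that such a person exists.
3. Record the rater of each mRS in the eCRF, so that any remaining self-rating or imbalance is visible.
4. Limit the Blinding section's conclusion to self-completed outcomes.
5. Separately, reconcile the Blinding section with item 2 on the CLCE-24 at T1. That score is the starting value for the CLCE-24 change analysis and is obtained differently in the two arms.

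**Cost.** Some calls move from nurses to researchers. The upper bound on all follow-up calls is 516 × 2 = 1,032 if every recruited patient is reached twice; the share nurses would have made is not stated. Masking may be incomplete, because patients can mention their hospital or the consultation. If the only available caller is a researcher who also delivered consultations, some self-rating remains. Even then the single route removes scoring by the nurse and any difference in mode.
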